#### Sample size

In order to determine the sample size, we assumed a moderate effect (*r* = 0.24 that corresponds to Cohen’s *d* = 0.5) of the intensity of programme use (*X*) on the change in symptoms of anxiety and depression (*Y*). Since this is a non-randomized study, we will use a set of covariates ***W*** to correct for selectivity in the uptake of the programme. In applying the G*Power 3 software [50] to determine the sample size, we assume that the effect of *X* corresponds to a 6% of explained variance of *Y* (equivalent to the moderate effect, since *R*^2^ = *r*^2^ = 0.24^2^ = 0.06) above the covariates ***W*** and assume a 6% reduction of the total variance in *Y* of the residual variance due to the use of covariates of ***W***, leading to a partial *R*^2^ = 0.06 or, equivalently, an effect size of *f*^2^ = 0.0638. Furthermore, setting *α* = 0.05 and the power of 1 – *β* = 0.80, the sample size calculation shows that 126 patients are needed. Patients will be considered as drop-out when they refuse to complete questionnaires. With an estimated attrition of 20% (i.e. 80% complete at least one follow-up questionnaire), we aim to include 158 patients.

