#### Quantitative data analysis

For each of the quantitative research questions, a separate analysis will be performed using log data from the E-health platform, data from the case registration forms that have been completed by the MHPs, and data from the four questionnaires:To what extent do patients use a tailored relapse prevention programme?

The use of the tailored relapse prevention programme will be described, focusing on different aspects of its use, such as the number of login sessions, the amount of time spent online, the number of completed modules, the number of diary entries, the number of sessions and the number of online and face-to-face conversations with the MHP. Descriptive statistics will be used to provide insight into these aspects of the use of the relapse prevention programme.2)What factors influence the use of the programme?

The use of the tailored relapse prevention programme may differ across patients, and may depend on age, education level and clinical situation. We will explore possible differences in usage between groups of patients systematically, considering sociodemographic factors, clinical symptoms and self-management strategies.3)What is the association between usage intensity and course of symptoms?

Descriptive statistics will be used to provide insight into course of symptoms for ‘high-use’ participants and ‘low-use’ participants. In order to analyse the association between usage intensity and course of symptoms, multiple regression analyses will be performed. We will first analyse the change in anxiety severity from baseline to follow-up (9 months) with the following independent variables: intensity of E-health use, number of diary entries and number of contacts with the MHP. We will repeat these analyses for the depression outcomes. In addition, analyses will be performed using ‘deterioration: yes or no’ as outcome variable. Deterioration is defined as an increase of 1 standard deviation on the IDS-SR and/or on the BAI. The standard deviation will be calculated using data from the NESDA study [48], the study from Kok et al. [49], and the present study. This analysis will be performed using a time-lag model, in which the outcome will be assessed using determinants from an earlier measurement (deterioration at time_*t*_ predicted by usage intensity at time_*t-1*_), since we assume that usage intensity might influence whether deterioration occurs at a later point in time.

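### The 20% attrition allowance counts patients with any follow-up questionnaire, but the 9-month change regression needs T9, so 126 analysable patients is a best case and power is likely to fall below 80%

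*Protocol article*

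**What the plan says.** The Sample size section of the protocol article fixes the test at "setting *α* = 0.05 and the power of 1 – *β* = 0.80" and reasons from a moderate effect of usage intensity on symptom change, "leading to a partial *R*^2^ = 0.06 or, equivalently, an effect size of *f*^2^ = 0.0638". From this, "the sample size calculation shows that 126 patients are needed". It gives no time point for the symptom change.

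Drop-out is defined by questionnaire refusal: "Patients will be considered as drop-out when they refuse to complete questionnaires". The recruitment target follows: "With an estimated attrition of 20% (i.e. 80% complete at least one follow-up questionnaire), we aim to include 158 patients". The follow-up questionnaires are at 3, 6 and 9 months (T3, T6 and T9; Data collection – measurements).

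The time point appears under Quantitative data analysis, research question 3: "We will first analyse the change in anxiety severity from baseline to follow-up (9 months) with the following independent variables". The predictors listed are E-health use, diary entries and MHP contacts, and the analysis is repeated for depression. A separate deterioration analysis (yes or no) uses a time-lag model. The article names no method for a missing T9 questionnaire.

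**The concern.** The two sections count different patients. The inflation to 158 treats as retained anyone who returns at least one of T3, T6 and T9. The regression outcome is the difference between T9 and baseline, so it is observed only for those who return T9. T9 completers are a subset of those with any follow-up. They can equal that group but cannot exceed it, and in a nine-month study with three follow-up waves they will usually be fewer.

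At stake is whether 158 is enough for the power stated for research question 3. If the number with an observed 9-month change falls below 126, the 80% overstates what that regression can detect.

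**Working it through.** **Inputs (Sample size section).** Two-sided α = 0.05 (the F test for a single predictor is equivalent to a two-sided t test), target power 0.80, partial R² = 0.06, required n = 126, attrition 20%, target 158.

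**Step 1: reproduce the 126.**
- Effect size: f² = 0.06 / (1 − 0.06) = 0.0638, as stated.
- Test: F test for the increase in R² from one predictor, with 1 and n − k − 1 degrees of freedom (k = total predictors) and noncentrality λ = f² × n.
- For k from 1 to 10, the smallest n with power of at least 0.80 is 125 or 126. At n = 126, λ = 0.0638 × 126 = 8.04 and power is 80.3%.
- Two alternatives do not reproduce the figure: a one-sided test gives 99, and a joint test of three predictors gives 175 to 176.

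The powered analysis is therefore a regression of one continuous change score per patient, testing one usage predictor. That is the form of the 9-month change regression. It is not the form of the deterioration analysis, which has a yes/no outcome and is time-lagged.

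**Step 2: reproduce the 158.** 126 / 0.80 = 157.5, rounded up to 158.

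**Step 3: the margin.** 158 × 0.80 = 126.4, so 126 patients are expected to have at least one follow-up. T9 completers number at most 126. One retained patient without T9 brings the count to 125.

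**Step 4: power over an assumed range of T9 completion.** The documents give no T9 rate, so the first column is an assumption. The calculation takes 158 enrolled, observed T9 outcomes only, f² = 0.0638 and k = 1. Using k = 10 changes power by no more than about 0.15 percentage points. The last column is 126 divided by the completion rate, rounded up.

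| T9 completion | n (158 × rate, rounded down) | λ = 0.0638 × n | Power | Enrolment for 126 T9 completers |
|---|---|---|---|---|
| 80% | 126 | 8.04 | 80.3% | 158 |
| 75% | 118 | 7.53 | 77.7% | 168 |
| 70% | 110 | 7.02 | 74.7% | 180 |
| 65% | 102 | 6.51 | 71.5% | 194 |
| 60% | 94 | 6.00 | 67.8% | 210 |
| 50% | 79 | 5.04 | 60.1% | 252 |

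A shortfall of one or two patients hardly matters: n = 125 still gives about 80%. The loss becomes material at around 70% completion and below.

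**The case against.** A reader might infer that fewer than 126 patients will certainly be analysable and that the 80% power is therefore not delivered. The documents do not support that. It needs a T9 completion rate below 80% and an analysis restricted to observed T9 values, and neither is stated. If everyone with any follow-up also returns T9, n is 126 and power is 80.3%. Weekly reminders to non-responders are planned. The handling of missing T9 data may sit in an analysis plan that is not shown, so its absence from an article is no fault.

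It can also be said that the Sample size section names no time point, that no analysis is labelled primary, and that the time-lag analysis can use patients with only earlier waves.

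A second tempting inference is that those lost at T9 would be the low users or those who worsened. Usage and questionnaires are both online, so a link is plausible, but nothing in the documents shows it. The point does not rest on it.

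These arguments limit how firmly the consequence can be stated. They do not remove the mismatch. The attrition definition and the 158 derived from it are both stated, and they do not fit the only described analysis that has the form of the power calculation. Imputing T9 from earlier waves would generally recover only part of the lost information, so it would not make the calculation right as written.

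**Conclusion.** The point holds in a limited form. The allowance is defined on any follow-up, while the matching regression needs T9. On the plan's own 80% assumption, 126 T9 completers is the ceiling, with no margin. Power for that regression is likely to fall below 80%, by an amount the documents do not determine: about 78% at 75% T9 completion, 75% at 70% and 68% at 60%.

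This rests on two assumptions: that some retained patients lack T9, and that the regression uses observed outcomes. It also rests on reading the 9-month change regression as the powered analysis, which the form of the calculation supports but the text does not say outright.

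The issue is moderate and not one that must be resolved before the study can stand. The design is observational, the Discussion gives acceptability and not efficacy as the aim, and this regression serves one of five research questions.

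**What to change.** In the Sample size section, define attrition as a missing T9 questionnaire, state the expected T9 completion rate, and restate the power for the T9 completers expected out of 158. This changes wording and one calculation and needs no extra patients. The cost is a slightly less favourable stated power. If 80% is to be kept for this regression, the last column of the table shows the enrolment needed at each assumed rate.

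Optionally, specify a repeated-measures model for anxiety, and separately for depression, using T3, T6 and T9, so that patients with any follow-up contribute. Usage would have to be measured before each outcome; otherwise nine-month usage would be set against a T3 score that precedes much of it. This model changes the target from 9-month change to an average or trajectory effect. It needs its own power basis, because 126 comes from a single-outcome test and a patient with only T3 says less about month 9. Having 126 contributors would not by itself restore the stated 80%.

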### Qualitative data

#### Data collection – measurements

The individual interviews and focus group interviews are conducted to assess implementation and satisfaction with the programme.

##### Individual interviews

Paired interviews will be conducted separately with patients and their MHPs in order to gain insight into both perspectives on one case. These paired interviews provide valuable insights regarding similarities and differences in experiences of MHPs and patients [51, 52]. Purposive sampling will be used to select patients and realise sufficient variation in our sample with respect to gender, age, severity of symptoms, and use of the programme [53]. Patients will be invited by email and telephone to participate in a semi-structured interview to evaluate their experience with the relapse prevention programme. If willing to participate, their MHP will be invited as well. The interviews will be conducted by two researchers, who will prepare the interviews by performing two test interviews. A senior researcher will provide supervision and participate in the analysis. We aim to conduct 12–15 interviews with patients and 12–15 interviews with MHPs. The final number of interviews depends on when data saturation is achieved.

A topic guide is developed to support the interview process [see Additional file 1]. This guide was drafted by the first author and reviewed by two experts, and inspired by the Consolidated Framework for Implementation Research (CFIR) [54]. Main topics are: experiences with the relapse prevention programme, use of the relapse prevention programme, useful and less useful aspects of the programme, and suggestions to improve the programme. Input from the E-health platform will be used, such as completed and uncompleted modules, use of the diary, and number of online conversations with the MHP. The topic guide will be evaluated and updated after conducting four interviews.

The MHPs of patients who participate in the interviews will also be invited by email and telephone to participate in an interview. Besides evaluating the programme (research question 5), implementation barriers and facilitators will be discussed in these interviews (research question 4), see Additional file 2 for the topic guide.

These interviews will be conducted in a setting selected by participants and will take approximately 45 min.

##### Focus group interviews

After completing the individual interviews, two focus group interviews will be conducted, one with 8–10 patients and one with 8–10 MHPs. The goal of the focus group interviews is to present, test and discuss preliminary findings and conclusions from the individual interviews. A focus group interview is appropriate for this situation, since the group interaction provides insight into topics of agreement and favourable and unfavourable topics, and experiences with the programme can be shared [55]. A moderator will lead the group discussion, and an assistant moderator will take notes, observe and keep track of the time [56]. The input from the individual interviews will be used in these focus group interviews, to discuss desirable changes to the E-health programme, in order to further improve its quality and usability. In order to obtain new perspectives on the evaluative data from the individual interviews, one half of the focus group participants will not have participated in a previous individual interview. The other half of the focus group members will be purposively selected from the patients and MHPs who previously participated in the individual interviews, where the selection is based on the diverging perspectives on using the relapse prevention programme. These focus group interviews will be conducted in a mental healthcare facility and will take approximately 90 min.

#### Qualitative data analysis

For each of the qualitative research questions, a separate analysis will be performed:4)What are barriers and facilitators in the implementation of the programme?

The barriers and facilitators in the implementation of the programme will be assessed through the semi-structured interviews and focus group interviews with the MHPs. These interviews will be audio recorded, and transcribed verbatim. Data will be sorted using the CFIR [54], which indicates five domains of implementation (intervention characteristics, outer setting, inner setting, characteristics of individuals and process). Data collection will alternate with data analysis and new topics will be discussed in the following interviews. Two researchers will independently openly code the first three interviews, compare the codes and draft a coding tree. The coding tree will be complemented through the following interviews. This data will be analysed using thematic analysis [57], which means that the interviews will be coded for themes, these codes will then be sorted and analyses will be performed using software programme MaxQDA. When reporting the data, quotations will be used to illustrate the findings.

During this process, multiple researchers will be involved in order to increase the validity and reliability [56]. From the beginning of data collection until the end of data analysis, detailed field notes will be documented, containing specific situations, reflections, and ideas and thoughts of the researchers [56]. In addition, a summary will be made of each interview, containing the most important findings.5)How do patients evaluate the program?

The evaluation of the programme will be assessed by the semi-structured interviews and focus group interviews with the patients. In addition, in the last follow-up questionnaire (T9), patients will be asked about their satisfaction with the programme and to rate every module they completed on a scale from 0 to 10. The data from the interviews and focus group interviews will be analysed in the same way as described above (research question 4). Data from T9 will be analysed using descriptive statistics.

## Discussion

Providing relapse prevention for anxiety and depression is important, since these disorders are often chronic and recurrent. In this study we will implement and evaluate a newly developed relapse prevention programme, specifically targeted at patients that are (partially) remitted from an anxiety disorder or depression. The mixed-methods approach in this study will provide valuable insights into how patients use the programme, what influences the use of the programme, how usage intensity influences symptoms and how patients evaluate the programme. In addition, information on implementation will be provided which may be relevant for broad implementation of the programme. The findings of this study can be used to further refine and adapt the programme as preferred by patients and MHPs.

A strength of this study is that the relapse prevention programme has been developed based on patient preferences and in close collaboration with patients. Additionally, this programme is not only web-based, but also supplemented by contact with MHPs. Earlier research suggests that E-health can be especially effective when accompanied by therapist contact [58]. By using log data to establish the usage of the programme, the actual use and usage behaviour can be determined [59]. Furthermore, by using mixed methods, a complete view on the use of the programme and its evaluation can be obtained [59].

This design is not appropriate to examine efficacy, since only within-group effect sizes can be determined, which might be considered a limitation of this study. However, the aim of this study was not to examine the efficacy of the programme, but its acceptability. If the programme is acceptable, a randomized controlled trial should be conducted to determine the efficacy of the programme.

## Abbreviations

ASI: Anxiety Sensitivity Index
BAI: Beck Anxiety Inventory
CBT: Cognitive behavioural therapy
CFIR: Consolidated framework for implementation research
DSM: Diagnostic and statistical manual of mental disorders
GET READY: Guided E-healTh for RElapse prevention in Anxiety and Depression
IDS-SR: Inventory of Depressive Symptomatology – self-report
MHP: Mental health professional
TiC-P: Trimbos/iMTA Questionnaire for Costs Associated with Psychiatric Illness
WHODAS: World Health Organization Disability Assessment Schedule
